#### Follow-up stage

At follow-up, CHVs will ask and seek for general danger signs and examine any complaints on the child. In addition, the systematic evaluation will be conducted to examine any cough, fever or diarrhea following the standard treatment and follow-up protocol. Anthropometric measurement weight and MUAC will be taken to determine any changes (gains) in the child. The CHVs will further conduct systematic evaluation to look for edema not detected at the general danger signs and appetite test. Children with either danger signs, failed appetite test, weight loss, diarrhea will be referred to the health facility, otherwise the CHVs will conduct treatment for MAMA or SAM as appropriate.

For SAM cases, during follow-up the RUTF will be provided for the next 7 days and if RDT is positive, ACT will be provided on the spot and twice daily for 3 days. Adelbanzole will be given if during the second visit the child is aged more than 12 months. In the case of MAM, the CHVs will give folic acid and continue RUSF for the next 7 days. The diversification and breastfeeding should be emphasized again at this point.

Furthermore, during follow-up all SAM children will be subject to weekly visit to CHVs for MUAC measurement and weight using the dosage scale, and collection of RUTF as per dosage scale will continue for a maximum of eight weekly visits if the child is progressing well, otherwise referral will be recommended in case of non-response to treatment. On the other hand, MAM children will be subject to bi-weekly (every 2 weeks) visits for MUAC measurement and collection of RUSF (1 sachet per day for 16 weeks for a maximum of eight visits if child is progressing well, otherwise the child needs to be referred). Table 5 outlines the follow-up procedure for both MAM and SAM.

**Table 5 Tab5:** Follow-up procedure for both MAM and SAM

Follow up	Discharge criteria		Action
1) SAM, MUAC < 11.5 cm			
Weekly visit to CHV for MUAC measurement and weight using the dosage scale and collection of RUTF as per dosage scale Maximum of 8 weekly visits if child is progressing well Two consecutive MUAC and/or weight measurements with no change or deterioration	cured	MUAC≥12.5 cm 2 consecutive green on MUAC	Discharge as cured
	defaulter	Misses 3 consecutive visits	Exclude from the study, Trace and admit as return defaulters but not for study
	Treatment failure	Two consecutive MUAC and/or weight measurements with no change or deterioration	Refer to health facility for further investigation
	/Non-response	Two consecutive MUAC measurements with no change of deterioration	
	Lost to follow up	Misses 3 consecutive visits and cannot be traced	Exclude from the study
2) MAM; 11.5 cm ≤ MUAC < 12.5 cm			
Bi-weekly visits (every 2 weeks) for MUAC measurement and collection RUSF (1 sachet per day for 16 weeks Maximum of 8 visits if cyhild is progressing well	cured	MUAC≥12.5 cm 2 consecutive green on MUAC measurement	Discharge as cured
	defaulter	Misses 3 consecutive visits	Exclude from the study, trace and admit as return defaulters but not for study
	Treatment failure/non-response	Two consecutive MUAC measurements with no change; deterioration on MUAC	Refer to health facility for further investigation
	Lost to follow up	Misses three consecutive visits and cannot be traced	Exclude from the study

All the activities during this intervention will be clearly documented using primary data collection tools and will be collated and for further analysis on the effectiveness of ICCM-CMAM integration.

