### Description of the counties selected for the trial

#### Turkana County

Turkana County, situated in North Western Kenya, is the largest of the 47 counties in Kenya with a total area of 77,000 Km^2^ administratively divided into seven sub counties namely; Turkana Central, Loima, Turkana South, Turkana East, Turkana North, Kibish and Turkana West. According to the latest, 2009, Kenya Population and Housing Census (KPHS) [15] and statistical estimates, the county has a population of 855,399, and expected to grow to 1,427,797 by the year 2017. The population of children under 1 year and those below 5 years is projected to reach 25,922 and 186,243 respectively by 2017.

Turkana is drought-prone and experiences frequent, successive and prolonged droughts virtually every year. Turkana’s harsh environment and historic underdevelopment has led to the highest poverty rate in Kenya at 94%, with significantly lower indicators for human development and service coverage than the rest of the country. According to the 2009 KPHS, less than one in five (18%) of the population can read and write, only 9% roads were tarmac and less than one in five households had access to improved sanitation [15]. The average distance to a hospital, health centre or dispensary is 50 km. Serious gaps in human resources further complicate service availability. Doctor to population ratio stands at 1:70,000 while nurse to population ratio is 1:5200 [16].

According to the SMART survey conducted in June 2015 covering all the livelihood zones in Turkana county (pastoral, agro-pastoral and formal employment/business/petty trade), about one in four (25%) children in the county are acutely malnourished. The rates of acute malnutrition in Turkana Central/Loima, North and South/East indicated a *very critical* nutrition situation, while the nutrition situation in Turkana West was classified as *critical*. The weighted Global Acute Malnutrition (GAM) for Turkana County was 21.2% and SAM rate was 5%.

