### Data collection procedures

#### Quantitative data

Quantitative data will be conducted at baseline to establish coverage of SAM and MAM treatment as well as other relevant nutrition and iCCM indicators. Data on treatment outcomes will be collected during the implementation. Further, end line quantitative data collection will be done to assess the coverage of SAM and MAM treatments as well as other relevant nutrition and iCCM indicators.

These data will be collected via quantitative household surveys. Building on our extensive experience with household nutrition surveys and iCCM, We shall use questionnaires to collect detailed information on socio-demographic and economic characteristics of the household, child characteristics including health, nutrition status and standard anthropometrics in every time period. Anthropometric data, will include child’s weight, presence of oedema, height and mid-upper arm circumference will also be collected, using standard protocol [19]. Additionally, CHVs will also be interviewed to obtain data that shall inform of their understanding and practice of the laid out protocol. The same information will be compared with data collected from mothers or caregivers of children in the clusters to gauge the treatment regime received compared to the laid out practice. Altogether an understanding of the effectiveness of this service will be obtained. These questionnaires to be used will be pre-tested before fielding the final survey. Furthermore, in the Kenya context, at the level of health facility, there are registers which are used to follow-up children with MAM/SAM cases. Those registers provide valuable information on the outcomes (recovery, defaulter and death). But, for the community-based management of malnutrition, we will use similar registers to record all the management of MAM/SAM cases which will also provide information on our outcomes. We will setup a tracking system which help us to randomly select our sample size of MAM/SAM cases and follow-up them till 4 months period at each time point.

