### Pre-implementation qualitative data collection stage (baseline)

Rapid qualitative methods including in-depth interviews, FGDs and KII will be conducted with various stakeholders. Targeted women will be those whose children have been /are being treated for acute malnutrition or are suffering from acute malnutrition, their spouses and other men whose children have been treated/are being treated for malnutrition, other stakeholders including implementing partners, Ministry of Health officials, County government and local community leaders.

The qualitative study will seek to answer questions regarding general knowledge attitude and practices with regards to child feeding and current treatment of MAM/SAM, challenges that hinder treatment of acute malnutrition, cost and time implications of the new model of treatment, and the barriers and facilitators that affect the MAM/SAM treatment outcome measures including average length of stay; average rate of weight gain; cure rate; mortality rates; default rates and transfer rate. The study will also qualitatively seek to establish the views of CHVs and other health workers on the effect of the integration of iCCM and management of acute malnutrition (SAM and MAM) on their workload as well as its likely effect on the quality of standard iCCM care. For the implementing partners, policy and decision makers, we will focus mainly on their recommendations for adaptation of the integrated program and their perceived role in it.

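### Table 5 has no category for death or clinical referral and excludes defaulters and lost children, so the case-fatality, cured and defaulted rates can lose the very children they should count

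*Protocol article*

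**What the plan says.** The Primary outcomes list includes the cured, case-fatality, defaulted and non-cured rates. The quantitative analysis section plans a clustered chi-squared test for recovery, case fatality and default.

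Table 5 (Follow-up stage) gives the ways an episode ends, for SAM and for MAM: cured, defaulter, treatment failure/non-response, and lost to follow-up.

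- Treatment failure/non-response: the action is "Refer to health facility for further investigation".
- Defaulter (three consecutive missed visits): for SAM the action reads "Exclude from the study, Trace and admit as return defaulters but not for study". The MAM row is equivalent.
- Lost to follow-up: for SAM the criterion is "Misses 3 consecutive visits and cannot be traced". In both panels the action is exclusion from the study.

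The text above the table adds a further exit: "Children with either danger signs, failed appetite test, weight loss, diarrhea will be referred to the health facility".

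On outcome capture, the Quantitative data section says of the facility registers: "Those registers provide valuable information on the outcomes (recovery, defaulter and death". It states that similar registers will be used for community care and will supply the outcomes. A tracking system will sample cases and "follow-up them till 4 months period at each time point". The baseline qualitative section lists among the treatment outcome measures "cure rate; mortality rates; default rates and transfer rate".

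**The concern.** Volunteers in the intervention arm will close episodes by Table 5. A child who dies at home stops attending. Unless someone reports or discovers the death, that child meets the missed-visits criterion and falls into one of the two rows that end in exclusion. A child referred for danger signs, failed appetite or diarrhoea matches no row, so nothing in the table says how that child, or a later death, is coded.

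Exclusion takes a child out of both numerator and denominator. For case fatality this can hide deaths. For the cured rate it removes children who are largely not cured and so raises the rate. For the defaulted rate it is self-defeating, since removing every defaulter leaves nothing to count.

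Recovery is also the outcome on which the trial was sized, against a 15-point non-inferiority margin. Default and loss are unlikely to be unrelated to outcome in this setting. Community units are chosen more than 5 km from a facility, and for Turkana the article states: "The average distance to a hospital, health centre or dispensary is 50 km".

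**Working it through.** **1. Table 5 against the other sections**

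| Event | Row in Table 5 | Action in Table 5 | Stated elsewhere |
|---|---|---|---|
| Death | none | none | primary outcome; facility registers record it |
| Referral for danger signs, failed appetite or diarrhoea | none | none | ordered in the Follow-up stage text; transfer rate named in the qualitative section |
| Non-response | yes | refer | not marked for exclusion |
| Default | yes | exclude, trace, readmit outside the study | primary outcome |
| Lost to follow-up | yes | exclude | no statement that tracking continues |

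Three missed visits take about 3 weeks on the weekly SAM schedule and 6 weeks on the two-weekly MAM schedule. A child can therefore be excluded well before the four-month point. The article does not say that tracking goes on after exclusion.

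**2. Inputs**

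The article gives no expected death, default or referral rate, so no bias can be computed from it. It does give 120 children per arm, 75% recovery, a 15-point margin and 5% attrition. The Appendix figure reproduces: (1.64 + 0.84)² × 2 × 0.75 × 0.25 / 0.15² = 102.51; × [1 + 23 × 0.005] = 114.29; / 0.95 = 120.3, stated as 120. The sample size is not in question here.

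**3. Cure rate when non-cured children are excluded**

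Observed rate = 0.75 / (1 − e), where e is the fraction excluded, none of them cured (assumed).

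- e = 5%: 0.75 / 0.95 = 78.9%
- e = 10%: 0.75 / 0.90 = 83.3%
- e = 15%: 0.75 / 0.85 = 88.2%

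The first value of e equals the plan's own attrition figure. At 10% the shift is 8.3 points, or 8.3 / 15 = 55% of the margin if it occurs in one arm only. Confined to the intervention arm, it flatters the intervention. Confined to the control arm, it penalises it. If both arms lose the same 10%, both rates read 83.3% and the null difference is unchanged.

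**4. Case fatality when some deaths are excluded with their children**

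With D = 120 × true rate and f the fraction of deaths excluded (both assumed), observed rate = D(1 − f) / (120 − Df).

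| True rate | Deaths | f = 25% | f = 50% |
|---|---|---|---|
| 1% | 1.2 | 0.75% | 0.50% |
| 3% | 3.6 | 2.27% | 1.52% |
| 5% | 6 | 3.80% | 2.56% |
| 10% | 12 | 7.69% | 5.26% |

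Example: at 3% and f = 50%, 1.8 / 118.2 = 1.52%. If all deaths are excluded, the observed rate is zero.

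**5. A side inconsistency**

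The Follow-up stage text refers a child on weight loss without further condition. The SAM panel of Table 5 reaches referral for treatment failure after two consecutive readings of MUAC and/or weight without improvement. The two may be meant as a clinical check and a discharge category, but the article does not say so, and they need to be reconciled.

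**The case against.** Table 5 is a follow-up procedure, not a definition of outcome capture. Capture is described in the Quantitative data section. A community register modelled on one that records death would plausibly record death, and sampled cases are tracked for four months. Tracing is part of the defaulter action and precedes a lost-to-follow-up classification, and tracing is when a home death would come to light. The article is also condensed: register codes and outcome definitions may be in the full protocol or analysis plan.

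Much of this stands, and it rules out three stronger readings that a reader might infer.

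- *All referred children lack an outcome.* Non-responders have a row, and no referral row orders exclusion.
- *Deaths necessarily drop out of case fatality.* The planned registers and tracking may catch them. Loss is a risk that the wording permits, not something it prescribes.
- *Case fatality is biased in favour of the intervention.* Table 5 sits under the intervention protocol, so this direction is plausible. But control children come from the same kind of remote units and are themselves referred, and a control child who dies before reaching the facility may be missing from its register too. The article does not say whether the exclusion rule applies to them.

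The objection does not dispose of the exclusion rule. That is a stated instruction, not a detail left for later. Nothing in the article says that an excluded child stays in the four-month tracking, how a death found on tracing is coded, or that a death after referral counts in the arm of enrolment.

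**Conclusion.** The point holds as a defect in outcome classification and retention. Table 5 omits death and clinical referral, and it excludes two groups of children that the primary outcomes need. Followed literally, it can remove unrecognised deaths from case fatality, raise the cured rate and empty the defaulted rate.

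The size cannot be derived from the article. Under assumed exclusions of 5 to 15% of children, none cured, a true 75% cure rate reads 78.9 to 88.2%. Under an assumed loss of a quarter to a half of deaths, a true 3% case fatality reads 2.27 to 1.52%. These figures describe a single arm. Neither the size nor the direction of the bias in the comparison is established.

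**What to change.** 1. In Table 5, replace exclusion of defaulters and lost children with retention for outcome. Whatever care they receive afterwards is a separate matter.
2. Add two outcome codes, died and transferred/referred, to Table 5 and to the registers.
3. State that vital status is ascertained at the four-month point already planned for every enrolled child in both arms, including defaulters and referred children, and that each child is counted in the community unit and arm of enrolment.
4. Compute the case-fatality, cured and defaulted rates on all enrolled children.
5. Reconcile the weight-loss referral in the Follow-up stage text with the two-reading criterion in Table 5. This review takes no position on which rule is right.

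The cost is a change of wording, two register codes and one status check per closed or referred child within the existing tracking. Some children will remain untraceable. They should be reported as such, by arm, and kept in the denominator.

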### Data collection procedures

#### Quantitative data

Quantitative data will be conducted at baseline to establish coverage of SAM and MAM treatment as well as other relevant nutrition and iCCM indicators. Data on treatment outcomes will be collected during the implementation. Further, end line quantitative data collection will be done to assess the coverage of SAM and MAM treatments as well as other relevant nutrition and iCCM indicators.

These data will be collected via quantitative household surveys. Building on our extensive experience with household nutrition surveys and iCCM, We shall use questionnaires to collect detailed information on socio-demographic and economic characteristics of the household, child characteristics including health, nutrition status and standard anthropometrics in every time period. Anthropometric data, will include child’s weight, presence of oedema, height and mid-upper arm circumference will also be collected, using standard protocol [19]. Additionally, CHVs will also be interviewed to obtain data that shall inform of their understanding and practice of the laid out protocol. The same information will be compared with data collected from mothers or caregivers of children in the clusters to gauge the treatment regime received compared to the laid out practice. Altogether an understanding of the effectiveness of this service will be obtained. These questionnaires to be used will be pre-tested before fielding the final survey. Furthermore, in the Kenya context, at the level of health facility, there are registers which are used to follow-up children with MAM/SAM cases. Those registers provide valuable information on the outcomes (recovery, defaulter and death). But, for the community-based management of malnutrition, we will use similar registers to record all the management of MAM/SAM cases which will also provide information on our outcomes. We will setup a tracking system which help us to randomly select our sample size of MAM/SAM cases and follow-up them till 4 months period at each time point.

#### Costing data

Collection on costing data for integrating nutrition into iCCM will be carried out from the health system’s perspective and focus on the costs incurred by the system (e.g. government, donors) for the delivery of this health intervention. Furthermore, we will explore the societal perspective by including costs for the caregiver e.g. the caregivers’ travel costs and lost labor time, societal/opportunity costs. Other research costs such as salaries of personnel doing research (field monitors/supervisors) will not be taken into account.

In this health intervention program, the costs incurred could be summarized into three components.

*Start-up costs or pre-implementation costs*. These are costs which are borne by the provider of the iCCM intervention program to launch the intervention. These include: community outreach (mass media campaigns, social mobilization, focus group discussion, behavioral change communication etc.), training of CHVs who will implement the intervention, venue rental costs, material/office supplies used for the training, lodging costs of trainer and transport costs (fuel, vehicles), refreshments, allowances/per diems, CHVs start-up medicines and tools kit. The financial report will be used to capture these costs.

*Recurrent costs* are costs of resources incurred repeatedly and consumed within a year of procurement. These include: human resources (salaries, stipends of CHVs, supervision of the CHVs), consumables (pens, office supplier, reporting tools etc.) and operating costs of vehicles (fuel, utilities). We will also use time and motion survey to estimate the weekly workload of CHVs and the average time spent in implementing the intervention. Furthermore, we will also collect information on the cost of drugs used for the diagnosed, treatment of diarrhea, pneumonia, malaria and diseases of malnutrition. The source of these activities is the financial report, time and motion survey, and direct interview with the provider of the intervention.

*Capital costs* are costs borne for inputs which have a useful of life longer than a year such as vehicles, buildings and equipment. The resources identified as capital costs are calculated taking into account that these resources are used for several years and their alternative uses (opportunity cost). We therefore estimate the capital costs on an annualized basis using the current value of these resources, useful life, discount rate of 3% and animalization factor.

The program manager or institutional perspective is the three components listed above. The societal perspective is more global since it includes the three components of cost listed above and other household costs incurred for participating in community-based management of malnutrition (time taken to feed the child suffering from MAM/SAM, additional food purchased to feed the child and other related cost incurred).

In order to account for the inflation, all the costs will be converted in constant prices using the GDP deflator for year 2019 for Kenya. Our base year of costing exercise will be 2019. Furthermore, we will explore whether integrating management of acute malnutrition into iCCM is cost effective using the decision rule based on WHO-CHOICE (Choosing Interventions that are Cost-Effective).

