Cognizant to global initiative, the Kenyan Government, after elaborate consultations with stakeholders and aligning within its community health strategy, has launched a five-year National Framework and Plan of Action for Implementation of iCCM in 2013 [11]. The iCCM strategy encompasses the community treatment of malaria, pneumonia and diarrhea by trained and properly supervised community health volunteers [11, 12]. The strategy also involves some aspects of maternal, child health and nutritional screening for children under 5 years and referral of cases of malnutrition to health facilities for further management.

Research evidence has shown that about 80% of children with severe acute malnutrition (SAM) who have been identified through active case finding, or through sensitizing and mobilizing communities to access decentralized services themselves, can be treated at home [13, 14]. Thus, integration of management of acute malnutrition with iCCM would have the potential to maximize synergy of the interventions and improve efficiency of resource utilization.

However, provision for home or community-based management of acute malnutrition is not included as part of the Kenyan iCCM framework. Furthermore; little is known whether the value obtained from integrating the management of acute malnutrition within iCCM is worth the resources invested in the implementation of this intervention program. Evidence on the potential impact as well as practical experiences on how to integrate nutrition (including community-based management of acute malnutrition) as part of an iCCM package is limited or scantly documented.

Therefore, we aim to test the feasibility and effectiveness of integrating management of acute malnutrition (both MAM and SAM) into iCCM including treatment outcomes, CHVs performance, and coverage elucidating the enabling factors and challenges of integration. Such local evidence could inform policy and strategies for scaling up effective coverage of nutrition interventions, and therefore will have a paramount significance in informing the potential impact, costs and cost-effectiveness of linking nutrition with iCCM in Kenya.

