#### Secondary research questions

The study will also explore a number of secondary research questions focusing on the process variables. The secondary research questions include:
Can CHVs effectively manage acute malnutrition at the community level?
To what extent can CHVs screen, give treatment and manage ready-to-use therapeutic food (RUTF), ready-to-use supplementary food (RUSF) and other iCCM commodities at community level?What are the experiences of the CHVs in using the simplified CMAM tools?What is the effect of integrating acute malnutrition on the CHV’s performance, in regards to workload and quality of care in the management of primary iCCM illnesses (diarrhea, malaria, and pneumonia)?What are the enabling factors and challenges in integrating management of acute malnutrition into iCCM?Is the integration of management of acute malnutrition into iCCM cost effective compared to the baseline system (traditional facility-based approach)?

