### Secondary outcomes

Treatment of fever, pneumonia and diarrhea.Quality of care (CHVs performance and workload)Challenges and enablers in the effective integration of management of acute malnutrition into iCCMCost-effectiveness analysis
Cost per child recovered (from both a program and a societal perspective)Incremental cost-effectiveness ratio for ICCM modelRange of costs within the sensitivity analysis

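### Only capital items are annualised, so launch costs with multi-year benefit would fall on the study period and overstate the integrated model's cost per child recovered

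*Protocol article*

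**What the plan says.** Under Costing data, the protocol article gives each of three cost components its own treatment.

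- **Start-up.** "These are costs which are borne by the provider of the iCCM intervention program to launch the intervention". The list covers outreach, training of the community health volunteers (CHVs), training venue and materials, trainers' lodging, transport (with fuel and vehicles named), allowances, and a kit of medicines and tools. The measurement rule is: "The financial report will be used to capture these costs".
- **Recurrent.** Salaries, stipends, supervision, consumables and vehicle running costs. Here the article adds that "we will also collect information on the cost of drugs used for the diagnosed, treatment of diarrhea, pneumonia, malaria and diseases of malnutrition".
- **Capital.** Inputs lasting more than a year, with vehicles, buildings and equipment as examples. "We therefore estimate the capital costs on an annualized basis using the current value of these resources, useful life, discount rate of 3" per cent.

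The components are then combined: "The program manager or institutional perspective is the three components listed above". The societal perspective adds household costs to the same three.

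Secondary outcomes lists "Cost per child recovered (from both a program and a societal perspective"), an incremental cost-effectiveness ratio (ICER) and a sensitivity analysis of costs whose content is not described. The economic question under Secondary research questions is: "Is the integration of management of acute malnutrition into iCCM cost effective compared to the baseline system (traditional facility-based approach")? Costing data says that the answer will be judged by a WHO-CHOICE decision rule.

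**The concern.** The reason given for annualising capital is that such resources are used over several years. Trained volunteers, a sensitised community and reusable tools also outlast the period in which they are paid for, yet they sit in the component that is taken as booked. Combining the components as described adds one year's share of capital to the whole launch outlay.

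The effect is one-sided. By definition launch costs are borne by whoever launches the intervention, while the comparator is an existing system. They therefore raise the integrated model's cost and would not be expected to cancel in the ICER. The result would describe the cost of a pilot's first year, whereas the Discussion looks ahead to scaling up at relatively low cost. A verdict under the WHO-CHOICE rule could be less favourable to integration for reasons of accounting alone.

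The classes also overlap: vehicles are named under both start-up and capital, so the same kind of item falls under two rules.

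**Working it through.** The article states no cost total, cost per child recovered or ICER, so there is no figure to reproduce. The only numerical input from the document is the 3% discount rate.

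**Assumptions, none of them in the document:** the useful life of start-up items, L; the start-up share s of the programme cost as charged; the charging of all start-up outlay to one year; and, for simplicity, that all of s is durable.

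**Step 1, annuity factor.** a(L) = (1 − 1.03^−L) / 0.03. One year's share of an outlay is 1/a(L).

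**Step 2, overstatement of annual cost.** Set the cost as charged to 1. With start-up annualised it becomes (1 − s) + s/a. The overstatement is 1/[(1 − s) + s/a] − 1. With the number of children recovered held fixed, the same percentage applies to cost per child recovered.

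| L (years) | a(L) | 1/a(L) | s = 10% | s = 30% | s = 50% |
|---|---|---|---|---|---|
| 1 | 0.9709 | 1.0300 | −0.3% | −0.9% | −1.5% |
| 2 | 1.9135 | 0.5226 | 5.0% | 16.7% | 31.4% |
| 3 | 2.8286 | 0.3535 | 6.9% | 24.1% | 47.8% |
| 5 | 4.5797 | 0.2184 | 8.5% | 30.6% | 64.2% |

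Worked example, L = 3 and s = 30%: 0.70 + 0.30 × 0.3535 = 0.806, and 1/0.806 = 1.241, or 24.1% too high.

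**Step 3, incremental cost.** If start-up outlay S falls on the intervention arm alone, full charging overstates the annual incremental cost by S × (1 − 1/a). That is 48% of S at 2 years (1 − 0.5226), 65% at 3 years (1 − 0.3535) and 78% at 5 years (1 − 0.2184). The percentage effect on the ICER cannot be given, because it also depends on control-arm costs and on the difference in effect, neither of which is in the document.

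**The case against.** The strongest reply is that no sentence says launch costs are expensed in full. The article names their source, and a condensed article may leave their handling to a fuller costing plan. Capital is defined by function, as inputs lasting more than a year, with its examples introduced as illustrations, so an analyst could move durable start-up items into that class. This stands in part: full charging is the natural reading, not a quoted rule. But the article does set out the method. It defines the classes, attaches annualisation to one of them, assigns training and outreach to another, and combines all three. An analyst who follows it would mix annualised and unannualised multi-year outlay.

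The size is also open to challenge. Share, life and charging period are all assumed. The Discussion names high attrition among CHVs as a challenge, which would shorten the life of training; at one year the problem disappears. That objection stands. Some of the kit is medicines, which should not be spread over years. That stands too, and limits the fix.

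A reader might go further and infer that drugs for malaria, pneumonia and diarrhoea are wrongly charged against nutritional recovery. The documents do not support this:

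- The article says only that drug cost information will be collected, not that all of it enters cost per child recovered.
- Under Intervention protocol, malaria treatment after a positive rapid test is part of the visit for severe acute malnutrition, so some of these drugs belong to the malnutrition episode.
- The Background says: "The iCCM strategy encompasses the community treatment of malaria, pneumonia and diarrhea by trained and properly supervised community health volunteers". If these drugs are costed alike in both arms, they cancel in the ICER.

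**Conclusion.** The point holds for start-up costs, conditionally. As written, annualisation covers capital inputs only, and launch outlay with multi-year benefit would be charged to the study period. That would overstate the integrated model's annual cost and cost per child recovered. It would probably also overstate the ICER, on the inference that the existing facility-based system carries no comparable launch cost.

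The direction follows from the text for any useful life of two years or more. The size does not: the range of about 5% to 64% rests wholly on assumed shares of 10–50%, lives of 2 to 5 years and a one-year charging period. It would be wrong to say that the cost per child recovered is overstated by a known amount.

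On drugs no error is shown. At most, the plan could say how drugs outside the malnutrition episode are to be apportioned. The point concerns a secondary outcome and leaves the primary comparison untouched, but it bears directly on the cost-effectiveness conclusion and should be settled before costs are analysed.

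**What to change.** Amend Costing data as follows.

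1. Annualise the durable start-up items (training, outreach, reusable tools) at the 3% already chosen, over a stated useful life. Leave start-up medicines and other consumables unannualised.
2. Vary that useful life in the sensitivity analysis already listed under Secondary outcomes, including a one-year life to reflect volunteer attrition.
3. Report full charging of start-up outlay as an alternative result, labelled as the cost of the launch period.
4. Place vehicles in one cost class only.
5. Optionally, state that drugs used outside the malnutrition episode are apportioned or costed identically in both arms.

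The cost is a few sentences of protocol text and spreadsheet work on data already planned. The drawback is that the useful life is a judgement, which is why it must be stated and varied.
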